## 2. OBJECTIVES

### Primary Objectives:

To determine energy expenditure and substrate oxidation in response to protein/carbohydrate and fat ratio of the diet

To determine sleep duration and sleep quality in response to protein/carbohydrate and fat ratio of the diet.

### Secondary Objectives:

To determine body composition in response to protein/carbohydrate and fat ratio of the diet

To determine body fat distribution in response to protein/carbohydrate and fat ratio of the diet

To determine (muscle) protein synthesis and regional muscle mass in response to protein/carbohydrate and fat ratio of the diet

### 3. STUDY DESIGN

[figure not shown]

**Figure 1:** Flow diagram of study design.

The study will have a parallel design and will consist of a short-term (1 week) and long-term (12 weeks) dietary intervention period.

Two days before the baseline measurement, subjects will be fed in energy balance (EB) with protein intake of 15En%. After the baseline measurement, subjects (n=40) will be randomly divided in two groups (2 x n=20). The two applied conditions will differ in the absolute protein content of the meals, including 5En% and 30En% from protein. Fat content will be kept constant in all three conditions regarding the possible effects of fat intake on fat oxidation, resulting in macronutrient compositions of the diets of En% Protein/Carbohydrate/Fat: 5/60/35 and 30/35/35. Both conditions will be compared with the baseline measurement when subjects are fed in energy balance with a macronutrient composition of 15/50/35 En% (Protein/ Carbohydrate/Fat). During the 12 weeks dietary intervention period, subjects will receive recipes prescribed by a qualified dietician. The 30En% protein group will receive recipes for high-protein meals and in addition protein supplements. The 5En% protein group will receive recipes for low-proteins meals and in addition carbohydrate supplements.

To determine energy expenditure and substrate oxidation, subjects will stay in the respiration chamber for 48 hours at baseline, after 1 week and after 12 weeks of an energy balanced diet. During the stay in the chamber, polysomnography will be used to measure wake and sleep phases continuously, in order to determine sleep duration and sleep quality. Every morning blood samples will be taken in fasted state to determine plasma concentrations of glucose, insulin and free fatty acids. Appetite and mood profiles will be measured hourly and before and after each meal, by anchored 100mm visual analogue scales and by POMS and STAI-state questionnaires.

At the start and after 12 weeks, 3-compartment body composition will be determined with the deuterium dilution technique combined with densitometry (BodPod). To investigate fat distribution MRI and  $^1\text{H}$ -MRS will be used. Abdominal fat will be assessed at baseline, and liver fat and intramyocellular lipid (IMCL) content, as well as the mass of the vastus lateralis muscle will be measured at baseline and after 12 weeks.

To assess dietary protein intake and thus compliance to the diet, subjects will complete 24-hour urine collections at the start, during their stays in the respiration chamber and at week 11. One week before the baseline measurement and at week 11 an accelerometer will be worn to measure habitual physical activity.

During the screening, after 6 weeks and after 12 weeks of high protein diet the glomerular filtration rate (GFR) will be estimated using the Modification of Diet in Renal Disease (MDRD) study equation (for detail see section 6.3).

After the final measurement in the respiration chamber the subjects are invited for a final test day in which (muscle) protein synthesis will be measured. This additional test day is not compulsory and subjects that do not want to participate can still take part in the rest of the study.

During the test day, subjects will receive a test-drink containing 20 g intrinsically labelled casein to be able to measure the effect of protein ingestion on muscle protein synthesis. This allows us to determine the true incorporation of amino acids from the ingested, intact casein into the muscle, taken into account the influence of digestion and absorption processes of a whole protein (24-27). Intrinsically labelled milk proteins were derived from milk that has been collected from cows that were infused with L-[1-C] phenylalanine (27). This procedure has been successfully used in human intervention studies by the research group of [name]. [name] (MEC 06-3-064, MEC 07-3-086, MEC 09-3-078.3, MEC 10-3-080), which has already resulted in multiple publications (24-27). Subsequently, plasma and muscle samples will be collected. Together with the use of an intravenous L-[ring-H5]phenylalanine, L-[1-C]-leucine and L-[ring-H2]tyrosine infusion, the digestion and absorption kinetics of the ingested protein, whole body protein balance and the fractional synthetic rate (FSR) of mixed muscle protein in the fasted and fed state in an *in vivo* human setting will be assessed.

[figure not shown]

**Figure 2:** time schedule of the additional test day.

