## SUMMARY

**Rationale:** Protein has been observed to increase satiety and energy expenditure to a greater extent than carbohydrate and fat and can therefore reduce energy intake. However, it still has to be confirmed if this effect is permanent or transient over a longer period of time.

Moreover, dietary intakes may significantly affect sleep when macronutrient intakes are manipulated. Since sleep deprivation has been recognized as a risk factor for obesity, improving sleep by a change in macronutrient intake would be promising in the treatment of obesity.

**Objective:** To determine energy expenditure and sleep in response to protein/carbohydrate and fat ratio of the diet over a short-term and long-term period of time.

**Study design:** The study will be conducted in a parallel design. Allocation of subjects to the two conditions is randomized.

**Study population:** Forty healthy male and female subjects with a BMI between 18-27 kg/m^2 and aged between 18-35 years will be included in the study. All subjects will be non-smoking, weight stable, and at most moderate alcohol users without sleeping problems. Subjects will be free of medication except for oral contraceptive use in women.

**Intervention:** The subjects will stay three times 48 hours in the respiration chamber: at baseline, after 1 week (short-term effect) and after 12 weeks (long-term effect) of dietary intervention. After baseline measurement (protein intake of 15 energy percent), two conditions will be applied: protein intake of 5 and 30 energy percent. Fat content will be kept constant.

**Main study parameters/endpoints:** The primary endpoints of this study are energy expenditure, substrate oxidation and sleep. The secondary endpoints of this study are body composition, fat deposition and muscle protein synthesis rate, expressed as fractional synthetic rate (FSR).

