The present study aims to determine energy expenditure, substrate oxidation and muscle protein synthesis rates with diets contrasting in protein content over a longer period of time. By determining the long-term effect of high protein and low protein diets it will be possible to elucidate if the effect of protein on energy expenditure is a permanent or transient effect, as well as the contribution of protein synthesis to the protein induced thermogenesis. Moreover, the study aims to determine the different effects of diets contrasting in protein content on sleep duration and sleep quality, measured by electroencephalography. We hypothesize that the diet with 30En% of protein will affect sleep, energy expenditure and will have a fat free mass sparing effect by increasing protein synthesis. The diet with 5En% of protein will not affect sleep, energy expenditure and will not spare fat free mass. By comparing subjects with different sleep duration and quality, it will be possible to confirm the fat free mass sparing effect of sleep.

As a secondary aim the present study determines body composition (including body fat content, fat mass and fat free mass), body fat distribution (including abdominal, liver and muscle fat) and (muscle) protein synthesis in response to diets contrasting in protein content.

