#### *Sleep*

During each stay in the respiration chamber, sleep will be monitored continuously via polysomnography. The subject is only allowed to sleep on the times stated by the investigator, so daytime naps and sleeping is not allowed, and will be controlled via the polysomnographic measurements. Polysomnography typically consists of 4 measurements: EEG, EMG, EOG and ECG. To measure brain activity (EEG) 6 electrodes are placed on the head. These electrodes provide a readout of the brain activity that can be "scored" into different stages of sleep (N1, N2, N3 which combined are referred to as NREM sleep, and rapid eye movement sleep or REM, and Wakefulness). In addition, to determine if sleep occurs and especially to determine when REM sleep occurs, 2 electrodes on the chin and 2

electrodes on the eyes are necessary to measure muscle activity (EMG) and eye movements (EOG). Finally, 2 additional electrodes are placed on the chest to monitor heart rate and cardiac function (ECG). The combination of these data will make it possible to determine sleep duration and sleep quality. Sleep quality represents the amount of minutes in which the subject is in sleep stage N3 plus REM sleep divided by the total duration of sleep.

Subjective feelings of sleep will be assessed before each meal in the respiration chamber using 100 mm VAS with questions on subjective feelings of napping, physical exhaustion, alertness, sleepiness and how satisfying the sleep was. Opposing extremes of each feeling are described at either end of the 100-mm horizontal line, and subjects mark the line to indicate how they feel at that moment. An example of this questionnaire is attached to the protocol.

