Filling out the questionnaires will take about a minute per questionnaire, in total 3 minutes.

*Melatonin and serotonin*

Urine will be collected during each 48h stay in the respiration chamber to measure 6-sulfatoxymelatonin (urinary metabolite of melatonin) and 5-hydroxy-3-indole acetic acid (urinary metabolite of serotonin). An enzyme-linked immunosorbent assay will be used to determine urinary 6-sulfatoxymelatonin and 5-hydroxy-3-indole acetic acid levels.

*Energy intake*

Our subjects are in overall energy balance, as they are weight stable for at least three months and not currently on a diet. Two days before the first stay in the respiration chamber and during all their stays in the respiration chambers, subjects will be fed in energy balance. Calculations will be based upon average daily energy requirements (DER). The daily energy requirement for the two days before the experiment will be estimated as 1.75 times the Basal Metabolic Rate (BMR) (53). BMR will be calculated with the equation of Harris and Benedict (54). The energy requirement in the respiration chamber will be calculated as 1.4 times the

measured sleeping metabolic rate (SMR) of the first night. The selected activity index is based on results of a study in which physical activity was determined in confined conditions (a respiration chamber) resulting in a mean PAL of 1.4 (calculated as 24-h energy expenditure/SMR) (55). Daily energy intake will be divided over three meals: breakfast 20%, lunch 40% and dinner 40%. Breakfast will be given at 08:30 hours, lunch at 13:30 hours and dinner at 18:30 hours. During the first stay in the respiration chamber, the macronutrient composition of the diet will be 15/50/35 En% (Protein/ Carbohydrate/Fat). During the second and third stay in the respiration chamber, the macronutrient composition of the diet will be 5/60/35 En% for the one group and 30/35/35 En% for the other group. The diets consist of normal food products, which are commercially available in normal Dutch supermarkets. The protein supplements for the diet with 30 En% of protein and the carbohydrate supplements for the diet with 5 En% of protein are commercially available. A qualified dietician will freshly prepare the meals in a qualified research kitchen, just before they are offered to the subjects.

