### **8.2 Univariate analysis**

The Statistical Package for the Social Sciences (SPSS) will be used to perform univariate analyses. Differences in energy expenditure, substrate oxidation, (muscle) protein synthesis and sleep between the two conditions (and baseline measurement) will be tested with one-way ANOVA with Bonferroni post hoc corrections. Changes in VAS ratings over time between and within groups will be tested with repeated-measures ANOVA with Bonferroni post hoc corrections. Multiple linear regression analyses will be performed to determine between subjects effects. All statistical tests will be two-sided and differences will be considered statistical significant if  $p < .05$ .

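### Change from the 15En% baseline within one arm cannot be attributed to that arm's diet; only the randomised 30En% versus 5En% contrast can carry conclusions about diet

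*Protocol*

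**What the plan says.** The Summary sets the sequence: "After baseline measurement (protein intake of 15 energy percent), two conditions will be applied: protein intake of 5 and 30 energy percent". It also sets the timing: "The subjects will stay three times 48 hours in the respiration chamber: at baseline, after 1 week (short-term effect) and after 12 weeks". Section 6.3.2 (Energy intake) fixes the order for every subject: "During the first stay in the respiration chamber, the macronutrient composition of the diet will be 15/50/35 En% (Protein/ Carbohydrate/Fat". No group receives 15En% at the second or third stay.

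The baseline serves as a comparator. Section 3 says "Both conditions will be compared with the baseline measurement when subjects are fed in energy balance". Section 8.2 says that differences in energy expenditure, substrate oxidation, protein synthesis and sleep "between the two conditions (and baseline measurement) will be tested with one-way ANOVA with Bonferroni post hoc corrections".

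Section 1 frames the hypotheses diet by diet: "We hypothesize that the diet with 30En% of protein will affect sleep, energy expenditure and will have a fat free mass sparing effect", and "The diet with 5En% of protein will not affect sleep, energy expenditure and will not spare fat free mass". Sleep is one of the main study parameters (section 6.1.1). Section 6.3.2 (Sleep) says "During each stay in the respiration chamber, sleep will be monitored continuously via polysomnography", and the electrode counts given there add up to 12 (6 head, 2 chin, 2 eye, 2 chest).

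**The concern.** A statement that one diet by itself does, or does not, change sleep or energy expenditure needs a reference condition. Here the only reference is the same subjects' 15En% stay. That stay differs from the later two in diet, but also in being the subject's first stay in the trial's chamber with electrodes attached, and in being 1 or 12 weeks earlier. Within an arm these differences always occur together, so no choice of test or error term can separate them.

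If subjects simply sleep better once they know the chamber, both arms improve on baseline. That would count for the 30En% hypothesis and against the 5En% hypothesis with no diet effect at all. A shift in the opposite direction to a true effect would hide that effect. Sleep is the outcome most open to habituation, but the same logic applies to 24-hour energy expenditure and to 12-week changes in body composition.

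**Working it through.** **1. Which contrast the sample size supports (section 4.4).** Inputs: diet-induced thermogenesis 14.6 ± 2.9% on 29% protein and 10.5 ± 3.8% on 9% protein, α = 0.05, power 0.90.
- Pooled SD = √((2.9² + 3.8²)/2) = √11.425 = 3.380.
- d = (14.6 − 10.5)/3.380 = 1.213, as stated.
- Two-sided two-sample t-test (noncentral t): power 0.894 at 15 per group and 0.913 at 16 per group. The stated 16 is reproduced, and 16/0.8 = 20.

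The trial is therefore sized for high versus low protein, not for either diet against 15En%.

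**2. What each contrast estimates.** Let S be the shift from first to later stay that all subjects share (order, habituation, time), and let D30 and D5 be the true diet effects relative to 15En%.
- Change in the 30En% arm: D30 + S
- Change in the 5En% arm: D5 + S
- Difference between arms: (D30 + S) − (D5 + S) = D30 − D5

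S cancels only in the last line. D30 and D5 cannot be recovered one by one, because no arm gives S alone.

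**3. Size, as an illustration.** The documents give no value for S or for its variability. Assumptions: S = 15, 20 or 30 min of sleep, SD of change 40 min, no diet effect, one follow-up stay.

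Paired test of one arm against its own baseline, noncentral t with d = S/40 (0.375, 0.5, 0.75), at 0.05/3 for three pairwise comparisons:

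| Evaluable per arm | S = 15 | S = 20 | S = 30 |
|---|---|---|---|
| 20 | 20% | 37% | 76% |
| 16 | 15% | 28% | 63% |

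With SD of change 60 min and 20 per arm these fall to 9%, 16% and 37%. With S = 10 min, SD 40 and 20 per arm the figure is 9%.

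Section 8.2 read literally: one-way ANOVA with three levels (40 baseline values, 20 per arm), pooled error and Bonferroni comparisons, simulated. The between-subject SD is 40/√(2(1 − r)), that is 40 min at a between-stay correlation r = 0.5 and 51.6 min at r = 0.7.

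| r (assumed) | S = 15 | S = 20 | S = 30 |
|---|---|---|---|
| 0.5 | 10–11% | 23–24% | 64% |
| 0.7 | 4% | 9% | 34% |

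These are lower because the literal test treats repeated measurements on the same subjects as independent, which makes it insensitive. They are not lower because the confounding is smaller.

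The between-arm t-test on change from baseline, in the same simulations, rejects in about 5% of trials at every shift.

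**4. Would a shared shift show itself?** Not reliably. With a paired test at 20 per arm, the two arms' results are independent given S. The chance of exactly the pattern that section 1 predicts (30En% significant, 5En% not) is p(1 − p): 0.20 × 0.80 = 16%, 0.373 × 0.627 = 23% and 0.759 × 0.241 = 18% for the three shifts, with no diet effect.

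**The case against.** The strongest reply is that this is a randomised parallel trial. Section 8.2 names the two conditions first and puts the baseline in parentheses, the sample size rests on high versus low protein, and the objectives in section 2 ask for the response to macronutrient ratio, not for change from 15En%. The unbiased comparison is thus already planned and powered. This stands. A reader might infer that the whole trial is confounded, and the documents do not support that.

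Other parts of the reply also stand. The protocol gives no evidence that habituation occurs or how large it is, and section 6.3.2 lets subjects sleep only at times set by the investigator, which limits drift in sleep duration. A seasonal shift is weaker still as an explanation: the second stay is one week after the first, subjects take part in pairs so entry is staggered, and nothing says that all baselines fall in one season. One might also infer that an unadapted first night will drive the sleep result. Each stay lasts 48 hours, the protocol does not say which night is analysed, and that choice is commonly left to the statistical analysis plan.

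It can also be argued that a shared drift would be visible, because both arms would move together while the between-arm test showed nothing. This stands only in part. With arms of 20, one arm often crosses the significance threshold and the other does not (step 4 of the working), and section 1 invites that pattern to be read as support for both hypotheses. Nor does the parenthesis in section 8.2 settle the matter, since section 3 plans the baseline comparison outright and a statement that 5En% has no effect can be judged only against 15En%.

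**Conclusion.** The concern holds for each diet's own effect against baseline, and only there. Within an arm, diet is fully aliased with stay order and elapsed time. That follows from the design and needs no assumption. How often it would mislead is not known: the rates of 20%, 37% and 76% (paired, 20 per arm) and of about 4% to 64% (literal ANOVA) rest on assumed shifts of 15 to 30 min, an SD of change of 40 min and correlations of 0.5 to 0.7, and smaller shifts or larger SDs give smaller rates.

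It would go too far to say that habituation will be credited to the diets. The documents establish that the two cannot be told apart within an arm, not that a shift exists or which way it runs. The randomised 30En% versus 5En% comparison remains valid. The point deserves a change to the plan because section 1 states hypotheses that the design cannot test.

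**What to change.** - **Sections 3 and 8.2:** state that conclusions about diet rest on the between-arm difference (30En% versus 5En%) in change from baseline at week 1 and at week 12. Report within-arm changes from the 15En% baseline as descriptive, without a claim about the individual diet.
- **Section 1:** replace the two per-diet hypotheses with hypotheses about that contrast. The question whether the protein effect is permanent or transient can still be addressed, by setting the between-arm difference at week 12 beside that at week 1.

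The cost is wording only: no extra arm, subjects or procedures. The trial gives up saying which of the two diets moved away from 15En%, but this design cannot establish that in any case. No change to the nights analysed is needed for this point, because the between-arm contrast already cancels a shift that both arms share.

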#### 6.1.2 *Secondary study parameters/endpoints*

- body composition (% fat, kg FM and kg FFM), which will be calculated from body volume and total body water using the combined equation of Siri (40). Body volume will be measured with a BodPod. Total body water will be measured with Deuterium dilution according to the Maastricht protocol (41).
- fat distribution (abdominal fat, liver fat and IMCL), which will be determined with MRI and H-MRS
- Regional muscle mass of the upper part of the lower limbs, which will be determined with MRI
- plasma concentrations of glucose (mmol/L), insulin (mU/L) and free fatty acids (FFA, mmol/L) which will be measured before each breakfast in the respiration chamber by drawing one blood sample of 10ml from the antecubital vein of the contra-lateral arm using venapunction
- physical activity (counts/min) one week before baseline measurement and one week before final measurement, which will be measured using a triaxial accelerometer for movement registration (TracmorD; DirectLife, Philips new wellness solutions, Amsterdam, The Netherlands) sensitive to a wide range of body movements.
- mood, feeling of hunger and satiety, which will be measured hourly and before and after each meal, by Visual Analogue Scales (VAS) and by Profile of Mood States (POMS) and State Trait Anxiety Index (STAI) questionnaires (42, 43).
- 6-sulfatoxymelatonin (urinary metabolite of melatonin, ng/day) and 5-hydroxy-3-indole acetic acid (urinary metabolite of serotonin, ng/day) will be measured
- muscle protein synthesis rate, expressed as fractional synthetic rate (FSR):

In order to determine the FSR, the following parameters will be measured in blood and muscle tissue:

- Plasma free phenylalanine and leucine concentration (expressed as  $\mu\text{mol/L}$ )
- Plasma enrichment of L-[ring- $^2\text{H}_5$ ]phenylalanine, L-[1- $^{13}\text{C}$ ]phenylalanine and L-[1- $^{13}\text{C}$ ]-leucine (expressed as mole percent excess (MPE))
- Muscle free and protein bound enrichment of L-[1- $^{13}\text{C}$ ]phenylalanine, L-[1- $^{13}\text{C}$ ]-leucine and L-[ring- $^2\text{H}_5$ ]phenylalanine (expressed as MPE)

- whole body protein turnover: Whole body protein turnover consist of the following rates:

- Exogenous phenylalanine rate of appearance and plasma availability of phenylalanine.
- Total rate of phenylalanine appearance and disappearance (= protein turnover)
- Endogenous phenylalanine rate of appearance (=protein breakdown)

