#### *Magnetic resonance imaging (MRI) and Magnetic resonance Spectroscopy (MRS)*

MRI and MRS are non-invasive and non-irradiant imaging techniques, which will be used to determine abdominal fat and muscle mass of the upper part of the lower limbs (MRI), muscle and liver fat (MRS).

An MRI (magnetic resonance imaging) scan will be performed with a whole body scanner (Intera, Philips Medical Systems) to quantify fat distribution and regional muscle mass. A single-slice breath-hold turbo spin-echo (TSE) sequence (turbo factor 5, echo time TE 12 ms, TR 200 ms, slice thickness 10 mm, field-of-view (FOV) 420-450 mm, total measurement time 11 s) is modified to suppress the water signal so that the images contain mainly the fat signal. The breath-hold technique is used to avoid any motion artifacts (ghosting due to the movement of subcutaneous fat regions with high signal intensity), which would cause difficulties during the data segmentation. This technique is performed to measure fat content in the subcutaneous abdominal and visceral fat. Detailed measurement of abdominal fat was described by Tintera et al. (48). Transversal images will be made from the upper part of the lower limbs. Muscle mass will be expressed as volumes (cubic centimeters), derived by using tissue area measurements from multiple images. MRI is a safe procedure with no

ionizing radiation and no known risks as long as the exclusion criteria (no electronic implants, no pacemakers, no metal fragments in the eyes, skin or body) are not met.

Image guided localized single voxel H-MRS will be performed in the m.vastus lateralis at the start and after 12 weeks. The measurements are performed on a whole body scanner (Intera, Philips Medical System, Best, the Netherlands) with a flexible surface coil wrapped around the upper leg. This technique is performed to measure fat content in the muscle (intramyocellular lipid; IMCL). Detailed intramyocellular lipid measurement is described by Schrauwen-Hinderling et al. (49). While fat content in the liver will be determined using an MRS protocol as described by Stefan et al. (50).

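### Abdominal fat is scheduled at baseline only but listed as an outcome of the diets, so no diet effect on it can be estimated

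*Protocol*

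**What the plan says.** Three places in the protocol make abdominal fat part of what the diets are meant to change.

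- Section 2, secondary objectives: "To determine body fat distribution in response to protein/carbohydrate and fat ratio of the diet".
- Section 1, closing paragraph, says what this covers: "body fat distribution (including abdominal, liver and muscle fat", again in response to diets that differ in protein content.
- Section 6.1.2 lists the endpoint: "fat distribution (abdominal fat, liver fat and IMCL), which will be determined with MRI and" MRS. It gives no time points.

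Section 3 is the only place that gives abdominal fat a time point. One sentence holds two schedules. The first clause begins "Abdominal fat will be assessed at baseline, and liver fat and intramyocellular lipid (IMCL) content". The second, which governs liver fat, IMCL and muscle, continues "as well as the mass of the vastus lateralis muscle will be measured at baseline and after 12 weeks".

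Section 6.3.2 (MRI and MRS) describes the abdominal scan. Of the water-suppressed breath-hold sequence it says "This technique is performed to measure fat content in the subcutaneous abdominal and visceral fat", and it gives a "total measurement time 11 s". No visit is attached to the abdominal scan there. The muscle spectroscopy, by contrast, is placed at the start and at week 12.

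Section 3 also states that the 40 subjects are randomised, 20 to each diet, once the baseline measurement is done.

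**The concern.** An outcome can show the effect of a randomised diet only if it is measured after the diet has begun. As scheduled, abdominal fat is measured once, before allocation. The introduction argues that the effect of protein intake on fat distribution is unknown and that visceral fat can be imaged by MRI. For the abdominal compartments the trial could not answer that question.

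There is also a risk of misreading. Because abdominal fat appears among the endpoints, a difference between the diet groups might be reported under the fat-distribution objective. With a pre-randomisation value, such a difference would reflect only how the allocation happened to fall.

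The loss could not be repaired later, because no analysis plan can recover a scan that was not taken.

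**Working it through.** The point is structural and needs almost no arithmetic. The protocol states no sample size, effect or precision for abdominal fat. Its one sample-size calculation (Section 4.4) concerns diet-induced thermogenesis and has no bearing here.

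**Step 1. Set the schedules side by side.**

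| Measure | Baseline | Week 12 | Source |
|---|---|---|---|
| Abdominal fat (MRI) | yes | not scheduled | Section 3 |
| Liver fat (MRS) | yes | yes | Section 3 |
| IMCL (MRS) | yes | yes | Sections 3 and 6.3.2 |
| Vastus lateralis mass (MRI) | yes | yes | Section 3 |
| Whole-body composition | yes | yes | Section 3 |
| Waist and hip circumference | screening | not scheduled | Sections 4.1 and 6.3.1 |

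**Step 2. Could the sentence in Section 3 mean both visits for abdominal fat?** The abdominal clause has its own verb and its own time. If the later words about baseline and week 12 also applied to it, its own mention of baseline would serve no purpose. The natural reading is two separate schedules.

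**Step 3. What can be estimated?** Let Y0 be abdominal fat at baseline, Y12 the value at week 12, and A the diet group.

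- Within-subject change, Y12 − Y0: not available, because Y12 does not exist.
- Week-12 difference between diets, mean(Y12 | 30En%) − mean(Y12 | 5En%): not available, for the same reason.
- Baseline difference between diets, mean(Y0 | 30En%) − mean(Y0 | 5En%): available, but its expectation is zero because A is assigned at random after Y0 is measured. Tested at the protocol's two-sided 0.05 level, it would be significant about 5% of the time by construction, whatever the diets do.

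**Step 4. Count the loss.** Planned post-randomisation abdominal values: 0 of 40. Fat-distribution components with no follow-up: 1 of 3 (abdominal fat; liver fat and IMCL are kept). The abdominal component itself covers two compartments, subcutaneous and visceral, and both are lost.

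**Step 5. Look for a substitute.** Whole-body fat mass is measured twice but does not separate visceral from subcutaneous fat. Waist and hip circumference, which Section 6.3.1 uses to describe fat patterns, are described only at screening. Liver fat and IMCL are different depots. None of these replaces a week-12 abdominal scan.

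**The case against.** The best defence is that baseline-only scanning was deliberate. Section 3 gives abdominal fat its own clause, Section 6.1.2 is a list of parameters without time points, and the objective in Section 2 names only body fat distribution in general, which liver fat and IMCL can still serve. On that reading abdominal fat describes the subjects and is not an outcome. This fails on Section 1, which names abdominal fat explicitly among the components to be determined in response to the diets.

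Other points stand, and they limit the finding.

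- It concerns one component of one secondary endpoint. Change in total body fat, liver fat and IMCL can all be estimated, and Section 1 puts particular weight on ectopic fat.
- Section 8 names no test of abdominal fat, so a misleading between-diet comparison is a risk and not a planned analysis.
- The baseline-only wording may be a drafting slip. Figure 1, the flow diagram, was not available for this check. If it shows a week-12 abdominal scan, it conflicts with the text of Section 3, which would still need correcting.
- The cost of adding the scan is partly inferred. The protocol gives 11 s for a single-slice sequence, but not the number of abdominal slices, the coil change or positioning time, or whether all week-12 imaging falls in one session.

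**Conclusion.** The protocol is wrong as written. Section 3 leaves a named component of a stated secondary endpoint without any post-randomisation value: 0 of 40 subjects, 1 of 3 components. No diet effect on visceral or subcutaneous abdominal fat can be estimated from the trial as scheduled. The primary endpoints, the sample size and the other fat-distribution measures are not touched.

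The conclusion rests on the plain reading of the sentence in Section 3, on the stated order of baseline before randomisation, and on the absence of any later abdominal scan elsewhere in the text. It does not depend on any numerical assumption.

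**What to change.** Reconcile Section 3 with Sections 1, 2 and 6.1.2 in one of two ways.

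1. **Measure it.** In Section 3, schedule abdominal fat at baseline and at week 12, alongside the thigh MRI already planned for week 12. Compare the diets on the week-12 value with the baseline value as covariate, for visceral and subcutaneous fat separately. At the stated 11 s per single-slice sequence, one slice in each of 40 subjects is 40 × 11 = 440 s, or about 7 minutes of acquisition over the whole trial. The number of slices is not stated. Assuming between 1 and 10 separate acquisitions, the range is 11 to 110 s per subject. Positioning, any coil change and segmentation of the images come on top.

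2. **Relabel it.** If baseline-only was intended, say so. Call abdominal fat a baseline descriptor, and remove it from the response aim in Section 1 and the fat-distribution endpoint in Section 6.1.2. This costs only a change of wording, but the trial then makes no claim about abdominal fat.

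The first option keeps the stated objective intact and is the better choice if the week-12 imaging is still to come. In either case Figure 1 should be checked against the corrected text.
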